### Statistical Analysis Plan

Primary analysis will use the intention to treat principle, assuming return to baseline values for non-completers. Differences between participants who completed and withdrew will be assessed using t tests for continuous variables and Fisher's Exact Test for categorical variables. We shall examine weight loss over time using a mixed-effects model with a random intercept and slope for each participant. This method controls for the non-independence in results from the same participant and allows for heterogeneity between participants. Potential co-variates (gender, Tanner Stage, baseline weight) will be assessed, and, if appropriate, incorporated into the model. We will examine the effects of losses of body weight and body fat on clinically important markers of disease risk (lipids, blood pressure, waist: hip ratio, insulin resistance) using analysis of covariance. Data generated from the psychometric questionnaires (self-concept, anxiety, self-esteem and quality of life) will be used as secondary outcome variables to examine the extent and nature of psychological distress in obese adolescents pre-treatment and mixed-effects models will be used to examine changes in these parameters and their relationship with weight and waist: hip ratio change. Statistical significance will be based on two-tailed tests, with p < 0.05 considered significant.

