### Ethical considerations

Lack of treatment for the obese child should not be an option as weight gain in those not treated is unrelenting. A recent meta-analysis of randomised controlled trials for treatment of overweight in children clearly demonstrates that control groups whether wait listed or only given written information consistently gained weight (2.1% increase in % overweight post treatment and 2.7% post follow-up) [36]. This increase in weight in control groups raises ethical issues around having a control group, especially in a clinical setting with children presenting for assistance with weight loss. We received ethical permission to delay treatment in a control group for 12 weeks after which we offer the program of their choice. These ethical issues will limit the ability to design trials with a control group remaining without intervention for lengthy study duration, especially in treatment seeking adolescents.

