### Sample size

Our sample size calculations were based on our primary comparison, the difference in change in BMI z-score between the low fat and reduced carbohydrate groups. In our feasibility study (n = 30), the mean (SD) of BMI z-score changes over 12 weeks were -0.20 (0.17) and -0.11 (0.08) for the low fat and reduced carbohydrate groups respectively. In order to observe a clinically important difference in change of BMI z-score between the two intervention groups of 0.09, with α = 0.05 and power of 80%, and assuming standard deviation of 0.12, we require 29 individuals in each intervention group to complete the study. Assuming that 20% of participants will drop out of the study (in our feasibility study our attrition rate was 17%), we will enrol 35 individuals in each of the diet intervention groups. If 12 participants enrolled to the control group complete the 12 week wait-list period, we will be able to detect a difference of change in BMI z-score of 0.13 between the control group and either of the diet intervention groups (α = 0.05, power = 80%). If we assume 20% of control-group participants will drop out of the study, we will need to enrol 15 individuals in the control group.

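### The 80% power is calculated on completers, but the primary analysis sets non-completers to baseline; on the plan's own figures its power is about 66%

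*Protocol article*

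**What the plan says.** The Sample size section names the primary comparison as "the difference in change in BMI z-score between the low fat and reduced carbohydrate groups". It takes feasibility-study mean changes over 12 weeks of -0.20 (low fat) and -0.11 (reduced carbohydrate), a "clinically important difference in change of BMI z-score between the two intervention groups of 0.09", an SD of 0.12, α = 0.05 and 80% power, and concludes that "we require 29 individuals in each intervention group to complete the study". It then allows for 20% dropout (17% was seen in the feasibility study) by enrolling 35 per diet.

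The Statistical Analysis Plan section says: "Primary analysis will use the intention to treat principle, assuming return to baseline values for non-completers". Testing is two-sided: "Statistical significance will be based on two-tailed tests, with p < 0.05 considered significant". The same section plans a mixed-effects model with random intercept and slope, but describes it for weight loss over time. It does not say that this model replaces the return-to-baseline rule for BMI z-score.

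**The concern.** The two sections describe different analyses. Adding participants so that 29 remain is the logic of an analysis that dropouts leave. Under return to baseline they stay in, each with a change of zero. That pulls each arm's mean towards zero and adds a cluster of zeros to the spread. The power quoted for the primary comparison therefore does not belong to the primary analysis, and the chance of missing the difference that the protocol calls clinically important is larger than the 20% a reader would take from it.

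In addition, each arm's expected mean becomes the completer mean multiplied by the proportion retained. The contrast between diets then mixes diet effect with retention, which matters if the two diets are not equally easy to stay with.

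**Working it through.** **Inputs** (Sample size section): completer mean changes m = -0.20 and -0.11; SD s = 0.12; dropout d = 20%; 35 enrolled per diet; two-sided α = 0.05. Reading -0.20 and -0.11 as completer means is an assumption. The section does not say so, but it applies the 0.09 to those who complete.

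**1. The plan's own figure.** With difference 0.09, SD 0.12 and 29 per arm, the standardised difference is 0.09/0.12 = 0.75. The two-sample t-test needs 28.9, so 29 per arm, and power at 29 is 80.1%. The stated figure reproduces, as a calculation on completers.

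**2. The stated primary analysis.** Each arm is a mixture: change with mean m and SD s with probability 1 - d, and zero with probability d.

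- Arm mean = (1 - d)m: 0.8 × -0.20 = -0.160 and 0.8 × -0.11 = -0.088. Difference in size 0.072.
- Arm variance = (1 - d)s² + d(1 - d)m².
- Low fat: 0.8 × 0.0144 + 0.16 × 0.04 = 0.01792, SD 0.134.
- Reduced carbohydrate: 0.8 × 0.0144 + 0.16 × 0.0121 = 0.01346, SD 0.116.
- Standard error = √((0.01792 + 0.01346)/35) = 0.0299; 0.072/0.0299 = 2.40.
- Power: 65.9% by noncentral t (68 degrees of freedom), 67.2% by normal approximation, 65.9% in 50,000 simulated trials.
- Enrolment needed for 80% under this analysis: 49 per diet.

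**3. Variants** (noncentral t unless stated).

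| Change to the inputs | Power |
|---|---|
| Dropout 17%, as in the feasibility study | 69% |
| Exactly 7 of 35 drop out per arm (simulation) | 68% |
| Feasibility SDs 0.17 and 0.08 in place of 0.12 | 59% |
| 37 enrolled per diet (29/0.8, rounded up) | 68% |
| 41 per diet: the abstract's 100 recruits shared pro rata to 35:35:15 (assumed) | 73% |

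**4. Unequal dropout.** The documents give no attrition by arm, so these splits are assumptions. Let both diets have a completer change of -0.155 (midway between -0.20 and -0.11), with 35 per diet and SD 0.12. The induced difference is 0.155 × (d₂ - d₁).

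| Dropout | Induced difference | Rejection rate (simulation) |
|---|---|---|
| 20% v 20% | 0 | 5% |
| 15% v 25% | 0.0155 | about 8% |
| 10% v 30% | 0.031 | about 18% |

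The same mechanism can hide a real effect. With the planned means, 30% dropout on low fat and 10% on reduced carbohydrate gives 0.7 × 0.20 - 0.9 × 0.11 = 0.041, with power of 26%. The reverse split gives 0.9 × 0.20 - 0.7 × 0.11 = 0.103.

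**The case against.** Return to baseline is explicit, prespecified and keeps everyone randomised. With equal dropout it holds the type I error at 5% and only shrinks the difference. That is correct, but it leaves the power statement unmatched.

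The 66% is conditional. If 0.09 were the difference across all 35 per diet with dropouts already counted and SD 0.12, power would be about 87%. The Sample size section does not say this, and its wording about completers points the other way.

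A reader might infer that the trial will report a false diet difference. The documents do not support that. The splits in step 4 are assumed, and the difference is false only if dropouts would have kept completers' losses. If they truly return to baseline, a diet that more adolescents stay on does have the larger effect across all randomised participants.

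A reader might also infer that the rule overwrites real week-12 values of people who stopped the diet but were measured. Non-completer is not formally defined, but both sections speak of completing, dropping out of or withdrawing from the study, so the natural reading is someone with no later measurement.

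A third tempting argument is that zero flatters control dropouts, since the Ethical considerations section says that "weight gain in those not treated is unrelenting". This does not bear on the comparison of the two diets, which is the one the sample size rests on.

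Finally, a mixed model does not settle what happened to dropouts. The abstract schedules outcomes at baseline, week 12 and week 24. Someone who leaves before week 12 contributes only a baseline value and is in effect credited with completers' change, which is further from weight gain than zero is. The choice of primary method is therefore partly a trade-off.

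**Conclusion.** The point holds as a mismatch between the stated power and the stated primary analysis. If 0.09 is the completer difference and dropout is 20% in both diets, power is about 66%, and the risk of missing that difference is about 34% instead of 20%. Across the variants in step 3 it runs from about 59% to 73% and never reaches 80%.

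The dependence on retention is a real property of the rule but a conditional risk. Its size rests on assumed dropout splits and on dropouts doing as well as completers, and with equal dropout there is no inflation of the type I error.

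**What to change.** Do one of the following.

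- **Keep return-to-baseline as primary.** Restate the power in the Sample size section for that analysis: about 66% with 35 per diet on the plan's own figures. This costs a sentence and an admission of lower power. Holding 80% would instead take about 49 per diet, 14 more in each.
- **Change the primary analysis.** Apply the mixed-effects model to all observed BMI z-scores of all randomised participants, and move return-to-baseline to a sensitivity analysis. This costs analysis wording only. The downside is the missing-at-random assumption, which for those leaving before week 12 amounts to assuming completers' change. A further sensitivity analysis with worse outcomes for dropouts should therefore go with it.

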**Methods and design:**

Eat Smart is a randomised controlled trial and aims to recruit 100 adolescents over a 2 1/2 year period. Families will be invited to participate following referral by their health professional who has recommended weight management. Participants will be overweight as defined by a body mass index (BMI) greater than the 90^th ^percentile, using CDC 2000 growth charts. An accredited 6-week psychological life skills program 'FRIENDS for Life', which is designed to provide behaviour change and coping skills will be undertaken prior to volunteers being randomised to group. The intervention arms include a structured reduced carbohydrate or a structured low fat dietary program based on an individualised energy prescription. The intervention will involve a series of dietetic appointments over 24 weeks. The control group will commence the dietary program of their choice after a 12 week period. Outcome measures will be assessed at baseline, week 12 and week 24. The primary outcome measure will be change in BMI z-score. A range of secondary outcome measures including body composition, lipid fractions, inflammatory markers, social and psychological measures will be measured.

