**Figure 1 F1:**
[figure not shown]
**Diagram of Study Flow**.

Overall Eat Smart provides a treatment protocol for use at a tertiary centre to assist obese adolescents seeking weight loss advice to reduce their weight. The first phase will evaluate the relative efficacy of two supported and structured 12 week weight reduction diets and an untreated control group:

(i) reduced carbohydrate (35% carbohydrate, 30% protein, 35% fat)

(ii) reduced fat (55% carbohydrate, 20% protein, 25% fat)

(iii) control - offered the dietary group of their choice (i or ii) after a 12 week waiting period

The primary outcome variable is reduction of BMI z-score. Secondary outcome variables are reduction in body fat and alteration in metabolic profile after 12 weeks. The psychological diagnostic interviews will document the extent and nature of psychological health in obese adolescents. In the second phase, with follow-up to 24 weeks, the relative efficacy of the low fat versus the reduced carbohydrate diet on BMI z-score.

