### Hypotheses to be tested

#### After 12 weeks

• There will be a difference in change in BMI z-score between the intervention diets and the control group.

• There will be a difference in the change of mean BMI z-score between the low fat and the reduced carbohydrate group.

• There will be a difference in the change of % body fat, markers of inflammation, insulin resistance and in lipid profile between the reduced carbohydrate group and the low fat group.

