#### After 24 weeks

• There will be a difference in mean change in BMI z-score in the low fat group compared to the reduced carbohydrate group.

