### Energy prescription

A tailored individual energy prescription for the intervention diets will be based on a 20% energy reduction compared to estimated energy requirements, which will be measured resting energy expenditure and physical activity level (PAL) derived from a 4 day activity diary. The 12 week intervention is designed to be an active weight loss phase. During the 'Maintenance Phase' (weeks 13-24), the goal is weight stability and maintenance of healthy behaviours.

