### Assessments and Measurement instruments

The laboratory technician conducting body composition measurements will be blinded to group allocation. The following assessments will be completed at M1 and M2 unless otherwise stated (see figure 1).

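### The mixed model is written for weight with one slope per participant, while the primary outcome is change in BMI z-score and the planned course bends at week 12

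*Protocol article*

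**What the plan says.** All places are in the protocol article.

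- **Outcome.** Below Figure 1 in Methods/Design: "The primary outcome variable is reduction of BMI z-score". The abstract agrees.
- **Hypotheses.** At week 12: "There will be a difference in the change of mean BMI z-score between the low fat and the reduced carbohydrate group". At week 24: "There will be a difference in mean change in BMI z-score in the low fat group compared to the reduced carbohydrate group". A further week-12 hypothesis sets the diets against control on BMI z-score, and another concerns body fat and metabolic markers.
- **Sample size.** It is built on "our primary comparison, the difference in change in BMI z-score between the low fat and reduced carbohydrate groups", with inputs taken from 12-week changes in the feasibility study.
- **Model.** In the Statistical Analysis Plan: "We shall examine weight loss over time using a mixed-effects model with a random intercept and slope for each participant". Sex, Tanner stage and baseline weight are the candidate covariates. The other mixed models in that section are for the psychometric scales.
- **Visits.** In the abstract: "Outcome measures will be assessed at baseline, week 12 and week 24".
- **Planned course.** The Energy prescription section reserves the first 12 weeks for losing weight. For weeks 13 to 24, "the goal is weight stability and maintenance of healthy behaviours".

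**The concern.** Two things do not fit together.

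First, the response. Participants are 10 to 17 years old and growing, so weight can rise while BMI z-score stays the same, and a stable weight can go with a falling BMI z-score. A model for weight with baseline weight as covariate estimates a difference in kilograms. It does not estimate the quantity in the hypotheses, and the 0.09 that the sample size section calls clinically important cannot be read off it. As written, the primary comparison has no model of its own.

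Second, the shape. One slope per participant describes a constant rate of change over 24 weeks, but the intervention is designed to produce change in the first half and little in the second. The article poses separate diet hypotheses at weeks 12 and 24, and one slope gives a single answer to both. At stake is whether the reported 12-week diet effect is the one the trial was sized to estimate.

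**Working it through.** **Inputs.** Sample size section: 12-week changes in BMI z-score of -0.20 (low fat) and -0.11 (reduced carbohydrate), difference 0.09, SD 0.12, α = 0.05, power 80%, 29 completers per diet. Statistical Analysis Plan: two-tailed tests. Abstract: visits at weeks 0, 12 and 24.

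**1. The plan's own figure.** Normal approximation: n = 2 × (1.960 + 0.842)² × 0.12² / 0.09² = 27.9, so 28 per arm. With the noncentral t distribution, power is 0.787 at 28 and 0.801 at 29. The stated 29 is reproduced, as the size for a two-group comparison of change.

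**2. Straight line through three equally spaced visits.** The least-squares slope is (y24 − y0)/24 per week, so the week-12 value drops out. The fitted 12-week change is 12 × slope = (y24 − y0)/2. With complete data and an intercept and slope for each diet, the random-intercept-and-slope model gives the same fixed effects as least squares.

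**3. Lose to week 12, then hold.**

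| | True change at week 12 | True change at week 24 | Fitted 12-week change |
|---|---|---|---|
| Low fat | -0.20 | -0.20 | -0.100 |
| Reduced carbohydrate | -0.11 | -0.11 | -0.055 |
| Difference (size) | 0.09 | 0.09 | 0.045 |

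The slope difference is 0.09/24 = 0.00375 per week; times 12 this is 0.045, half of 0.09. The fitted gap between the lines at week 12 is (0 + 0.09 + 0.09)/3 = 0.060, but this includes a spurious baseline gap of 0.060 − 0.045 = 0.015.

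If the diets are forced to share a baseline, the fitted difference is 0.045 to 0.046 (50% to 51%). That range covers assumed intercept SDs of 0.2 to 0.6, slope SDs of 0 to 0.008 per week and residual SDs of 0.03 to 0.085.

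**4. If the difference does not persist exactly.** Let the week-24 difference be f times the week-12 difference. The fitted share is f/2.

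| f | 0.75 | 1 | 1.25 | 2 |
|---|---|---|---|---|
| Fitted share of the true week-12 difference | 38% | 50% | 62% | 100% |

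Only f = 2, a diet difference that keeps growing at the same rate, gives the right week-12 value.

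**5. Power.** The fitted 12-week change is half of each participant's 24-week change, so its SD is halved as well. If the SD of the 24-week change is also 0.12 (an assumption), the test sets 0.045 against 0.06, the same ratio as 0.09 against 0.12. Power at 29 per arm is then 0.815 by the normal approximation, or 0.801 by t.

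A simulation of 300 trials agrees. It used 29 per diet, SD of true change 0.10 and error SD 0.047, so the SD of observed change is √(0.10² + 2 × 0.047²) = 0.12; the intercept SD of 0.4 is assumed. The slope test rejected in 78% of trials, the week-24 t test in 81% and the week-12 t test in 83%. The simulation error on 78% is √(0.78 × 0.22/300), about 2 percentage points.

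**6. Scale.** The article gives no effect size in kilograms, so the consequence of modelling weight cannot be sized. The factor f/2 is the same on either scale.

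**The case against.** The strongest reply is that the sentence on the mixed model describes only its random part. A random slope can stand beside a categorical visit term, and then the week-12 contrast is unbiased. The coding of time is a detail that a full protocol or analysis plan may hold. This stands: a reader might infer that the primary estimate will be halved, but the article does not fix the linear fixed term that this needs.

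Nor does the article label the mixed model as primary. Its statement on the primary analysis concerns intention to treat and setting non-completers back to baseline, and the 29 per arm matches a simple comparison of change. This stands too, but no other model is named for the diet comparison of BMI z-score.

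It can also be said that weight loss is loose wording for the BMI z-score outcome. That is possible, but the candidate covariate is baseline weight as well.

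A further reply is that stable weight in growing adolescents implies a falling BMI z-score, so a flat course after week 12 is not assured. That is fair for each arm taken alone. However, a further fall common to both diets cancels in the difference, and only the ratio f matters.

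Three stronger readings are tempting and not supported:

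- **Loss of power.** The standard error shrinks with the estimate, as step 5 shows. Setting 0.045 against an SD of 0.12 would be wrong.
- **A model that cannot be identified.** The assessment section says "The following assessments will be completed at M1 and M2 unless otherwise stated", which might suggest two visits only. But it defers to Figure 1, which is not available here, and the abstract gives three visits.
- **Control slopes mixed with later treatment.** The control hypothesis stops at week 12, and nothing says that later control data enter the model.

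**Conclusion.** The mismatch of response needs no assumption: the section names weight, while the primary outcome, the diet hypotheses on BMI z-score and the sample size use another variable.

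The mismatch of shape is conditional. It requires a linear fixed time-by-diet term and week-24 data in the same model. The fitted 12-week difference is then half of the week-24 difference: 0.045 instead of 0.09 if the difference persists, and about 38% to 62% of the true value for f between 0.75 and 1.25. The slope test then addresses the week-24 hypothesis. What suffers is the size and meaning of the week-12 estimate, not materially the power. The sample size draws on 12-week changes, so week 12 is the natural time for the primary comparison, although the sentence that defines it gives no time point.

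Severity: should be fixed.

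**What to change.** In the Statistical Analysis Plan section:

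- Make BMI z-score the response, with its baseline value as a covariate or as the first visit in the model.
- Treat time as a category (0, 12, 24 weeks) with arm-by-visit terms. A piecewise line with a knot at week 12 would also serve.
- Name low fat minus reduced carbohydrate at week 12 as the primary contrast, and the same contrast at week 24 as the second.
- Use control data to week 12 only.
- Keep weight as a secondary outcome.

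The cost is small. For the two diets, 2 × 3 = 6 visit means replace 2 × 2 = 4 line parameters. If an unstructured covariance is chosen, it has 6 terms instead of the 4 of a random intercept, random slope, their covariance and a residual. No data are needed beyond the week-24 measurement that the abstract already promises.

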### Allocation to groups

Treatment allocation will depend on gender and Tanner Stage (pubertal stage). Weighted randomisation will be used so that the participants will be allocated to the treatment group that minimises the gender/Tanner Stage imbalance between groups with a probability of 0.8 and will be conducted by the study statistician ([name]). Participants will be informed as to which group they have been assigned at their baseline assessment and if they are in the active diet groups, an immediate appointment with a study dietitian will be made. The control group will be given an appointment to attend in 12 weeks time when they will be offered the intervention treatment of their choice.

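### Sex and Tanner stage steer the allocation but enter the model only under an undefined condition, and baseline BMI z-score is not a candidate covariate although its change is the primary outcome

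*Protocol article*

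**What the plan says.** Under Allocation to groups, each participant is to be "allocated to the treatment group that minimises the gender/Tanner Stage imbalance between groups with a probability of 0.8". Sex and Tanner stage are therefore design factors.

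Under Statistical Analysis Plan, the model is introduced by "We shall examine weight loss over time using a mixed-effects model with a random intercept and slope for each participant". The covariate rule follows: "Potential co-variates (gender, Tanner Stage, baseline weight) will be assessed, and, if appropriate, incorporated into the model". The section does not say what would make a covariate appropriate, who decides, or when.

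The abstract names the primary outcome: "The primary outcome measure will be change in BMI z-score". The Sample size section takes as its primary comparison "the difference in change in BMI z-score between the low fat and reduced carbohydrate groups", "assuming standard deviation of 0.12", with no allowance for covariates. Baseline BMI z-score is not among the candidate covariates.

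**The concern.** Three features of the covariate rule do not fit the rest of the design.

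1. **Allocation and analysis are not tied together.** Balancing the arms on a prognostic factor makes the treatment difference less variable from trial to trial. A model without that factor still counts its variation as noise and reports the larger, unadjusted standard error. The estimate is not biased, but the interval is too wide and power is lost. This trial is planned at 80% power, so it has little to spare.

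2. **The rule has no criterion.** Three optional covariates give 2³ = 8 possible models. Without a stated rule, a reader of the results cannot tell whether the reported model was chosen independently of the treatment effect.

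3. **The baseline measure does not match the primary outcome.** Baseline weight suits a model of weight loss. In participants aged 10 to 17, weight also reflects age and height, so it is an imperfect stand-in for baseline BMI z-score when the outcome is change in BMI z-score.

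**Working it through.** **Inputs from the protocol.** Difference 0.09, SD 0.12, two-sided α = 0.05, power 80%, 29 completers per diet arm, enrolment 35 + 35 + 15 = 85 (Sample size); minimisation on sex and Tanner stage with probability 0.8 (Allocation to groups).

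**Input not in the protocol.** R², the share of variance in the outcome explained by the covariates. It is assumed here to be 0, 0.1, 0.2 or 0.3.

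**Step 1: reproduce the plan's figure.** For two means with SD 0.12 and difference 0.09, the normal approximation gives 28 per arm. The t-test gives power 0.787 at 28 and 0.801 at 29. The stated 29 reproduces as an unadjusted calculation.

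**Step 2: what omission does if balance were perfect.** The true standard error shrinks by √(1 − R²) and the reported one does not. The actual size is 2 × [1 − Φ(1.96/√(1 − R²))], which is 0.039, 0.028 and 0.019 for R² = 0.1, 0.2 and 0.3.

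**Step 3: what omission does under the planned scheme.** Allocation with probability 0.8 balances imperfectly, so it was simulated: 85 participants, target 35:35:15, total SD 0.12, 4,000 runs per setting, diet arms compared. The simulation also assumes equal numbers of each sex, a spread over five Tanner stages, R² shared equally between the two factors, and complete data.

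| Assumed R² | Size, factors omitted | Size, factors included | Mean reported SE, omitted | True SD of estimate, omitted | SE too large by |
|---|---|---|---|---|---|
| 0 | 0.048 | 0.048 | 0.0286 | 0.0286 | 0% |
| 0.1 | 0.040 | 0.049 | 0.0287 | 0.0274 | 5% |
| 0.2 | 0.035 | 0.053 | 0.0287 | 0.0261 | 10% |
| 0.3 | 0.019 | 0.043 | 0.0287 | 0.0245 | 17% |

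The reported SE agrees with 0.12 × √(2/35) = 0.0287. The Monte Carlo error of a size near 0.05 is √(0.05 × 0.95/4,000) = 0.003, so the third decimal should not be read closely.

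**Step 4: what this means for power.** In the same simulation, with a true difference of 0.09 and about 35 per diet arm:

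| Assumed R² | Power, factors omitted | Power, factors included |
|---|---|---|
| 0 | 0.87 | 0.87 |
| 0.1 | 0.89 | 0.91 |
| 0.2 | 0.90 | 0.94 |
| 0.3 | 0.90 | 0.96 |

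With the planned 29 completers per arm and a residual SD of 0.12 × √(1 − R²), the t-test power of an adjusted analysis is 0.80, 0.84, 0.88 and 0.92 for R² = 0, 0.1, 0.2 and 0.3.

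**Step 5: what the open rule permits.** A second simulation used two arms of 35, close balance on sex and Tanner stage, no treatment effect and 20,000 runs per setting. It assumed R² of 0.1 or 0.2 for the two factors and 0, 0.1 or 0.2 for baseline weight.

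| Way of choosing covariates | Type I error over the settings |
|---|---|
| All three always included | 0.049 to 0.051 |
| Each kept if p < 0.05 against the outcome, ignoring treatment | 0.047 to 0.050 |
| Smallest treatment p-value of the 8 models | 0.058 to 0.077 |

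The inflation comes from choosing by the treatment result, not from screening as such.

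**The case against.** **The factors are not excluded.** The rule names both and would admit them when appropriate. If assessment meant a joint 5% F-test in 70 diet-arm participants with 2 to 5 degrees of freedom (an assumption), the factors would be detected in about 51 to 68% of trials at R² = 0.1, 89 to 96% at 0.2, and 99% or more at 0.3. The larger losses in the tables would then seldom occur. This stands as a limit on size. It does not remove the point, because the document does not say that this is the test.

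**R² may be small.** BMI z-score is already standardised to reference data and the change covers 12 weeks. This stands: at R² near zero, omission costs nothing.

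**A reader might infer more than the text supports.** One inference is that the intervals will come out too wide. That requires the factors to be both prognostic and left out, and the document settles neither. Another is that covariates will be chosen after inspecting the results. The text says they will be assessed but gives no timing, and a screen blind to treatment keeps type I error near 5%. The two harms also pull in opposite directions: omission makes the test conservative, while favourable selection makes it liberal.

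**Baseline weight fits the sentence it follows.** The model is described for weight loss, and for that outcome baseline weight is a natural covariate. This stands. The mismatch is with the primary outcome, not within that sentence.

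**An article condenses.** A full plan may define the covariates. But the article states a rule, and a plan that fixed the covariates in advance would have to replace that rule rather than fill a gap in it.

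**Conclusion.** The point holds in a conditional form. The factors that drive allocation are optional in the analysis, with no criterion, and the baseline value of the primary outcome is not on the covariate list.

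The cost of omission runs from nothing at R² = 0 to standard errors about 17% too large and a size of about 0.019 at R² = 0.3. The treatment estimate is not biased. The range of R² is an assumption throughout. Separately, the discretion could raise type I error to about 0.06 to 0.08, but only if the model were picked for its treatment result, which the wording allows and does not prescribe.

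This is worth correcting because the remedy uses data already collected for the allocation. It is not a fatal flaw.

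**What to change.** State, before outcome data are seen, that the primary model for BMI z-score includes sex and Tanner stage (grouped if some stages are sparse) for every participant, whatever their observed significance. State also how baseline BMI z-score enters, in one of two ways:

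- as a covariate in an ANCOVA-type model of follow-up values or of change; or
- if baseline is one of the responses in the random intercept and slope model, through a baseline mean common to all arms, with sex-by-time and Tanner-by-time terms. Adding baseline BMI z-score as a covariate there would use the same measurement twice.

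Remove the conditional inclusion step. Keep baseline weight and any other covariate set as sensitivity analyses.

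The cost is a few degrees of freedom among 85 enrolled participants and a short restatement of the model, which at present is described for weight loss rather than BMI z-score. No further data are needed, and the sample size stands as calculated, since adjustment can only be credited once R² is known.
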